#### Phase 2: Set-up and training (3 months)

The intervention will be centrally co-ordinated by a community engagement team at UEL. A co-host community organisation will be recruited within each intervention site to support the local delivery of the intervention. Co-host organisations must meet certain criteria in order to be involved, for example: experience of managing, supporting and developing outreach teams; demonstrable experience of working with vulnerable groups including black and ethnic minority communitie; strong links to local community groups and organisations and statutory health servicesSix to eight local people will be recruited in each site as voluntary antenatal care champions, to engage directly and indirectly with women and families, and specific groups and organisations from their community, to raise awareness of the value and benefits of early antenatal care and how and when to access care. The antenatal care champions will receive training for this role (which will involve input from a midwife) on the antenatal care system, including referral pathways and the purpose and benefits of antenatal care. Champions will also be trained in presentation and communication skills, ongoing practice reflection, adult and child safe-guarding, and health and well-being coachingCo-host organisations and antenatal care champions in each site will work collaboratively with the UEL community engagement team and the research team to build on the detailed profiles and mapping of community assets for each intervention site, and to further develop their local outreach plans for intervention implementation, which will engage the whole system within each ward (e.g. schools, children’s centres, GPs, pharmacies, faith groups)A communications strategy and materials for the intervention messages, based on the outputs from the co-design workshops will be developed. The co-host organisations and antenatal care champions will also be part of the decision-making about whether and how the intervention messages ought to be tailored for each site

#### Phase 3: Implementation (6 months)

Implementation of the intervention will take place, in each of the sites, immediately after the development phase. As this will be co-produced and locally tailored, the outreach and engagement plans in each site may vary.

Antenatal care champions are likely to engage with their local communities about antenatal care, particularly women who are vulnerable to later service access, through: presenting and discussing information with groups (e.g. at community events, evening classes, faith groups); one-to-one sessions, where antenatal care champions will engage with local people directly and indirectly in places of high footfall (e.g. GP surgeries, pharmacies, shopping centres); informal, opportunistic outreach, building on existing networks and relationships within the community.

We will use a staggered approach, with implementation taking place first in three ‘pathfinder’ sites before starting in the remaining seven sites, in order that intervention development and delivery can benefit from some initial learning.

### The comparator

Normal maternity care promotion and practice will continue in the 10 electoral wards randomised to the control arm. All participating providers of maternity services are free to engage in additional actions to enhance early booking of antenatal care that affect populations in the electoral wards in either arm of the study.

### Outcome measures

Based on the hypothesis that the intervention will promote earlier booking of care, particularly by those most at risk of late booking (as per the pathways shown in Fig. 1), the primary outcome is the proportion of pregnant women in each ward who have attended their antenatal booking appointment by the end of the 12th completed week of their pregnancy. Secondary outcome measures are: the proportion of women who have attended their antenatal booking appointment by 10 weeks and 0 days of pregnancy; antenatal admissions; emergency caesarean rates; gestation and weight at delivery; smoking at booking appointment and at birth; feeding method at discharge. Outcomes will be measured using anonymised routine hospital data. Outcomes data, covering periods of 6 months, will be extracted by trust informatics staff at three time points. These time points are as follows: time point 1 (baseline) – women giving birth who were at least 13 weeks pregnant at the point that any intervention-related activities commenced; time point 2 (first follow-up) – women giving birth 2–7 months after the end of intervention delivery; time point 3 (second follow-up) – women giving birth 8–13 months after the end of intervention delivery. Further data on age, ethnicity, housing tenure, parity and deprivation will be provided along with the outcomes data.

The study will not require names, NHS numbers, dates of birth, addresses or postcodes. In order to ensure complete anonymisation, trust informatics staff will re-code potentially identifying individual level data; for example, age and ethnicity, into broad categories, ensuring this categorisation does not compromise any proposed analyses. The name of each electoral ward will be replaced by a unique ward-specific ID code that is not known to staff in the PCTU who will be analysing the data. In addition, an unblinded member of the PCTU data management team will liaise with informatics staff in each trust to ensure that secure data transfer methods are understood and used when transferring data from the trust to the PCTU. They will then make the data accessible to their data management colleagues who will remain blind to study site. The data management team will ensure the secure storage of study datasets for statisticians to conduct their analysis. A pilot of the outcomes data transfer process will be conducted across the study sites to ensure that procedures are deliverable by informatics staff and fit for purpose. A collaborative approach involving the research team, informatics staff and site PIs, to finalising the exact list of outcomes and the data transfer processes will be taken.

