**Fig. 1 Fig1:**
[figure not shown]
Logic model for the Community REACH intervention

The Community REACH study is one component of a wider programme of research, the REACH (Research for Equitable Antenatal Care and Health) Pregnancy Programme. With high priority given to public and practitioner involvement, the Programme is focussed on improving access to, and experience of, antenatal care (Hayes 2012) [22]. The University of East London (UEL) is the lead academic partner. Organisations working with UEL on the Community REACH study include: University College London (UCL) Institute of Education providing trials expertise and management; the Pragmatic Clinical Trials Unit (PCTU) at Queen Mary University of London providing data management, statistical support and quality assurance; UCL conducting the economic evaluation. Uscreates, a design agency with a social focus, supported the initial co-design and communication strategy of the intervention. The study runs from 1 April 2015 (when NHS Research Ethics Committee approval was received) to 11 October 2019 (the end date of the REACH Pregnancy Programme).

This paper was written after funding and approvals were received for the Community REACH study, participating NHS trusts were enrolled, randomisation of study sites and co-design workshops were completed, but prior to the intervention set-up and collection of any trial data.

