### Recruitment and selection of clusters for randomisation

For both substantive and pragmatic reasons NHS trusts in north and east London and Essex were targeted for recruitment to the study. The inclusion of an out of London area (Essex) is intended to enhance the generalisability of findings. Six NHS trusts agreed to take part, from which eight hospitals providing NHS maternity care (three providers from one large trust) enrolled in the study. NHS trusts were required to commit to providing routine maternity data for randomisation and assessment of outcomes as part of the participation agreement. Any trust unable to commit to this was not able to participate.

The research team identified 20 electoral wards eligible to include in the study, distributed across the geographical areas served by the participating hospitals. This identification process required informatics staff, already responsible for managing routine maternity data in each participating hospital, to extract retrospective ‘gestation at booking’ data for women using the maternity services of these hospitals during a defined recent 6-month period. Routinely this maternity data is organised by postcode. In order to render it non-identifiable for study purposes, the informatics staff converted the postcode data to its corresponding electoral ward name using a postcode-to-ward database sourced from local authorities and provided to the informatics staff by the research team. Informatics staff transferred the data to the research team in a dedicated study database sent in an encrypted form via email. A pilot of this data transfer procedure was completed in one hospital, in order to ensure that all processes could be operationalised and audited.

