## Analysis

### Trial outcomes

A cluster-level analysis, appropriate to the analysis of matched cluster randomised trials, will be used with the maternity care providers for the NHS trusts participating in the study as fixed effects. We will use intention to treat principles. We will include individual level prognostic covariates if appropriate and ward-level estimates of baseline levels of outcomes as covariates. These will be chosen in advance of any analyses being conducted and documented in a full analysis plan. In additional analyses we will explore the use of instrumental variable techniques to incorporate some process measures as mediators of effect. Our primary analyses will consider primary and secondary outcomes data pertaining to births in the period 2–7 months post intervention start. Further secondary analyses will be conducted using data for births in the period 8–13 months post intervention completion to explore the maintenance of any effects and trends. A small number of sub group analyses may also be conducted using Stata software (version 14; StataCorp, College Station, TX, USA).

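### The baseline cohort (time point 1) suits the two booking outcomes but not the birth-related secondary outcomes, for which it is post-randomisation, possibly part-exposed and short of preterm births

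*Protocol article*

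**What the plan says.** The Outcome measures section sets one extraction scheme for every outcome: "Outcomes data, covering periods of 6 months, will be extracted by trust informatics staff at three time points". Time point 1, the baseline, is "women giving birth who were at least 13 weeks pregnant at the point that any intervention-related activities commenced". Time point 2 is "women giving birth 2–7 months after the end of intervention delivery". Time point 3 is likewise defined by date of birth alone.

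The primary outcome is the proportion of women who have "attended their antenatal booking appointment by the end of the 12th completed week of their pregnancy". Booking by 10 weeks 0 days is a secondary outcome. The other secondary outcomes are "antenatal admissions; emergency caesarean rates; gestation and weight at delivery; smoking at booking appointment and at birth; feeding method at discharge".

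The Trial outcomes part of the Analysis section plans to include "ward-level estimates of baseline levels of outcomes as covariates", and its primary analyses cover both primary and secondary outcomes. The choice of covariates is to be documented in a full analysis plan.

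On timing, the end of the section on the development of the study says the article was written when "randomisation of study sites and co-design workshops were completed, but prior to the intervention set-up and collection of any trial data". The only outcome-type data described as taken before randomisation come from ward selection, where informatics staff were asked to "extract retrospective ‘gestation at booking’ data for women using the maternity services of these hospitals during a defined recent 6-month period".

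**The concern.** A baseline covariate should be settled before the intervention can act on it. A woman already 13 weeks pregnant has either booked by 12 weeks or not, so the rule achieves this for booking. The birth-related outcomes are still open at that point. They arise over the following months, while activity runs in the intervention wards only, and the protocol describes no other baseline for them.

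Two things are at stake, both for secondary outcomes only. First, if the intervention affects these women at all, adjusting for the result removes part of any later effect. Second, a cohort defined by a minimum gestation on a fixed date loses early births as the window runs on, whereas the follow-up cohorts have no such condition. Baseline gestation and birth weight then describe a different population of births from the one at follow-up.

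**Working it through.** The protocol gives no figure on this point to reproduce, so the check works from its definitions.

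**1. Order of events.** A woman pregnant on the commencement date gives birth after it. Phase 1 mapping, street engagement and workshops took place in the intervention sites, so allocation was already known. Baseline births are therefore after randomisation whichever phase starts the clock.

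**2. Which outcomes are settled at 13 weeks.** Booking by 12 completed weeks and by 10 weeks 0 days: settled. Admissions, emergency caesarean, gestation, weight, smoking at birth and feeding at discharge: not settled (admissions only in part). Smoking at booking is also open for women who had not booked by 13 weeks.

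**3. Overlap with implementation.** Inputs: a 6-month data period (Outcome measures), a 3-month Phase 2, and a 6-month Phase 3 that follows at once (The intervention). From 13 weeks to a birth at 39 weeks is 26 weeks, so the data period fills roughly the 6 months after commencement.

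- Clock starts at Phase 2: 6 − 3 = 3 months of the window fall in implementation, about half.
- Clock starts at Phase 1: the overlap is max(0, 3 − d) months, where d is the time from the first Phase 1 activity to the start of Phase 2. The article does not give d. If d is 3 months or more, the overlap is nil.

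**4. Truncation.** A birth at gestation g weeks, t weeks after commencement, qualifies only if g − t ≥ 13, that is t ≤ g − 13. With births spread evenly over 26 weeks from commencement (an assumption), the share kept is min(1, (g − 13)/26).

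| Gestation at birth | Calculation | Share kept |
|---|---|---|
| 30 weeks | 17/26 | 65% |
| 34 weeks | 21/26 | 81% |
| 36 weeks | 23/26 | 88% |
| 37 weeks | 24/26 | 92% |
| 39 weeks or more | 26/26 | 100% |

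A birth before 37 weeks needs t < 24, so the last two weeks of the window can contain no preterm birth.

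**5. Effect on a preterm rate (illustration only).** The documents give no gestation distribution. Assume preterm births split 6%, 10%, 14%, 25% and 45% at 26, 30, 33, 35 and 36.5 weeks. The share kept is (0.06×13 + 0.10×17 + 0.14×20 + 0.25×22 + 0.45×23.5)/26 = 21.355/26 = 82%. Assume term births split 8%, 17%, 32%, 28% and 15% at 37.5, 38.5, 39.5, 40.5 and 41.5 weeks; about 99% are kept. A true preterm rate of 8% then appears as 0.08×0.82/(0.08×0.82 + 0.92×0.99) = 6.7%. True rates of 6% and 10% appear as about 5.0% and 8.4%.

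**6. Scale at ward level.** Take 145 births per ward and ICC 0.005 from the sample-size section; the ICC is for booking, so applying it to birth outcomes is an assumption. The sampling standard error of an 8% rate is √(0.08×0.92/145) = 2.3 percentage points, against a truncation shortfall of 8.0 − 6.7 = 1.3 points. The reliability of a ward baseline is 145×0.005/(1 + 144×0.005) = 0.725/1.72 = 0.42. If the covariate slope is about that size, less than half of any exposure effect in the baseline passes into the adjusted contrast.

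**The case against.** The strongest case against the point has five parts.

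- **Start of the clock.** The definition refers to any intervention-related activity, and Phase 1 is presented as part of the intervention. The natural start is therefore Phase 1. The window would then cover brief street engagement, one workshop per ward, any gap, and set-up, with little or no implementation. This stands. A reader might infer that half or all of the baseline was exposed to the intervention, but the wording does not support that as the leading case.
- **Size of the exposure bias.** The messages concern early booking, and women past 13 weeks are mostly beyond that step. Late bookers prompted to attend sooner are the main exception. This stands: the bias is probably small, and the covariate slope shrinks it further.
- **Truncation and the arm contrast.** A reader might infer that losing preterm births biases the treatment comparison. It does not: the same rule applies in both arms, and a common shortfall is absorbed in the adjustment. Ward-level sampling noise is also larger than the shortfall.
- **Before–after displays.** A reader might foresee a spurious rise in preterm birth between baseline and follow-up. The cohorts would indeed differ, but the protocol plans no such comparison.
- **Deferral to the analysis plan.** The choice of covariates is left to that plan, so some birth outcomes may not be adjusted for this baseline. This stands in part. The cohort definition, however, is fixed here, and an analysis plan cannot use births that were never extracted.

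What the objection does not remove is that, as written, the baseline for these outcomes is neither pre-randomisation nor defined like the follow-up cohorts. If women who had already delivered by the commencement date were meant to be included, the text does not say so.

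**Conclusion.** The point holds for the birth-related secondary outcomes only. Their planned ward-level baseline is measured after randomisation and may be partly exposed: about 3 months of overlap with implementation if the clock starts at Phase 2, and less, possibly none, if it starts at Phase 1. Any resulting bias is probably small and towards the null.

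The preterm shortfall follows directly from the definition. Its size rests on even births over a 26-week window from commencement, and the preterm-rate illustration rests on an assumed gestation spread. Its consequence is a somewhat weaker covariate and baseline gestation and weight that are not comparable with follow-up. Provided both wards of a pair share the same commencement date, it is not a bias between arms.

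The inference that the primary analysis is compromised would be wrong: the 13-week rule does its job for both booking outcomes. Priority: minor.

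**What to change.** For the non-booking outcomes, define baseline as births in the 6 months ending the day before the first intervention-related activity, with no gestation floor, and use that as the ward-level covariate. State which activity starts the clock. Use the same calendar window for both wards of a pair, since control wards have no commencement date of their own and implementation is staggered. Smoking at booking can go with this group.

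Keep the present cohort for the two booking outcomes. If a single extract is preferred, the earlier window can serve all outcomes.

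The cost is one additional or shifted date range in a retrospective extraction from routine records, and a slightly older baseline. The article says no trial data had been collected when it was written, that outcome data collection follows the end of intervention delivery, and that the outcome list and transfer processes were still being finalised. On that account the change could be made before extraction.

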### Power and sample size

In our Programme Development Grant research, we analysed routine data from the maternity service at Newham University Hospital, which contained the corresponding postcode for each pregnancy in Newham from the period April 2007 to January 2011. We calculated by ward the variation in cluster size and the proportion accessing antenatal care by the 12th completed week of pregnancy as the basis for estimation of intra-cluster correlation coefficient and our sample size calculation. To detect an increase in antenatal booking by 12 weeks gestation from 75% to 82%, with 90% power at the 5% significance level requires at least 751 individuals in each trial arm. To account for clustering (ICC = 0.005, mean cluster size 145, matching correlation = 0.1) requires nine clusters in the intervention group and in the control group, which equates to 1450 women per trial arm. Because this sample size is relatively small, and to guard against a substantial loss of power if a cluster is lost for any reason, we added one cluster to each group. As described, pairs of clusters were matched by the hospital used by those in the ward seeking maternity care and by baseline rate of antenatal booking by 12 weeks. This has been measured per ward and collected pre-randomisation.

### Process evaluation

Ongoing formative evaluation work will be conducted alongside Phases 1 and 2 of the intervention, in order to inform the development of the intervention structure, activities and materials. Research team members will conduct observations and interviews to document and analyse the activities in each intervention site during the stages of community engagement, co-design, intervention set-up and training of antenatal care champions. The UEL community engagement team will provide records on intervention set-up in each site, and co-host organisations will provide records on recruitment of antenatal care champions.

A process evaluation will be conducted for Phase 3 of the intervention, to explore its implementation. This integral process evaluation will run alongside the impact evaluation.

Process data will be used to examine intervention implementation, acceptability and reach, issues of context, as well as hypothesise possible causal pathways, in order to facilitate interpretation of outcome data. In line with recent Medical Research Council (MRC) guidance on process evaluations for complex interventions [26], this component of the trial will also enable refinement of the intervention logic model (see Fig. 1).

The process evaluation has four specific components. These are:Documentation and analysis of the local social contexts in intervention and control sites

The mapping process described above in Phase 1 of the intervention will be expanded by the research team to document and analyse the local social context of the intervention and control sites and their main maternity providers, in order to identify events and influences that may hinder or support intervention implementation, or affect study outcomes. Information will also be recorded on all previous and current interventions/innovations regarding antenatal care that have been developed by maternity services, local authorities or community organisations for people living in the study sites2.Documentation and analysis of intervention activities

Intervention activities will be documented and analysed for each site. Members of the research team will observe up to two purposively selected events in each of the intervention sites, where antenatal care champions engage with their local community about antenatal care. The UEL community engagement team and the co-host organisations will provide detailed records of intervention delivery and progress.3.Interviews with antenatal care champions, co-host representatives and other stakeholders

The experiences of those taking part in the co-production and delivery of the intervention, and their perceptions regarding its impact on their communities, will be explored through qualitative research interviews. Up to 40 people, across three to four intervention ‘case study’ sites (final numbers dependent on data saturation), will be purposively sampled for individual interviews. Participants will be interviewed at the beginning and again towards the end of the intervention delivery phase. In the first interview, interviewees will be asked about their motivations for getting involved with the intervention, their expectations for how the intervention may be received within their local communities, their experiences and perspectives on the training process, and their early experiences with delivering the intervention messages around antenatal care. The second follow-up interview will be conducted with each participant approximately 6 months following their first interview, to address experiences with delivering the intervention and perceived intervention acceptability within the community. We will also aim to conduct interviews with those who cease their involvement with the intervention delivery while it is ongoing, in order to explore reasons for stopping. Interviews will also be conducted with local community midwives to gain insight into local maternity service provision and local barriers/enablers around access to antenatal care within the intervention site. Interviewees will receive a £10 voucher as reimbursement for their time. The qualitative research interviews will explore the social contexts within which the intervention is implemented, building a richer picture of intervention delivery and mechanisms of impact. The number of interviews to conduct in the remaining intervention sites, and who to interview, will be decided pragmatically and judiciously based on the findings from earlier sites.4.Survey to assess exposure to the intervention and its influence

A sample of 400 women across the 20 trial sites will be surveyed to assess reach, exposure to and acceptability of the intervention. The survey will be conducted with women attending appointments at antenatal booking clinics 3 months following the start of the implementation of the intervention. We will aim to conduct this with an approximate ratio of 3:1 intervention to control women surveyed. Hospital staff will identify eligible women, when they attend the clinic, based on their postcode. Women who agree to participate, will be provided with the survey in written, self-administered form, with the offer of researcher or bilingual health advocate support where required. The survey will be translated into other languages that are common to women using that particular maternity service. The survey will not contain sensitive or personal questions regarding the woman’s pregnancy, but rather will focus on the woman’s first point of contact in her antenatal care pathway, whether she had heard of the intervention and whether it had any effect on her decision-making about the timing of antenatal care initiation. Participants will receive a £5 voucher as a ‘thank you’ for their participation.

Women who would like additional time to make a decision about participation in the survey will be provided with a link to an online version that they can complete at a future date. On completion they will be invited to send their address by email to the research team in order that a £5 voucher can be posted to them.

